## Abstract

**Background:**

Neurogenic bladder is defined as a dysfunction of the bladder resulting from damage to the central or peripheral nervous systems. Its treatment is based on a progressive therapeutic escalation, rapidly involving invasive therapeutic procedures such as repeated intradetrusor injections and surgery. Given the risk of repeated general anaesthesia in children, there is a need for non‐invasive treatment for young patients who do not respond to or have adverse effects from oral anticholinergic treatment. The ‘Place de l’OXybutynine Intravésicale chez le Patient Enfant Neurologique’ (POXIPEN) trial aims to assess the efficacy of intra‐vesical oxybutynin on bladder capacity in a sample of French children with neurogenic bladder.

**Study Design:**

The POXIPEN is a multicentre, randomised, double‐blind, placebo‐controlled trial.

**Endpoints:**

The primary outcome is change in maximal bladder capacity after treatment. Secondary outcomes include changes in voiding, urodynamic and ultrasound parameters. We will also assess changes on quality of life and usability of the product.

**Patients and Methods:**

We aim to randomly assign 60 children with neurogenic bladder secondary to spina bifida and deemed non‐responders to first‐line treatment with oral anticholinergics, to receive intravesical oxybutynin (IVO) or placebo for 4 weeks. Recruitment will start in September 2025. It will be the first prospective study to evaluate the efficacy of IVO in children, with a high level of evidence provided by its design. If IVO proves effective, it could lengthen the delay in therapeutic escalation to invasive procedures, thereby reducing the risk of complications associated with general anaesthesia in children with neurogenic bladder.

**Trial registration:**

This trial is registered with the European Union (EU) Clinical Trials Information System (CTIS) under EU CT Number: 2022–501 902–36‐00 (approved 09.01.2025) and ClinicalTrials.gov under identifier NCT07027020 (registered 18.06.2025).

Abbreviations(S)AE(Serious) Adverse EventCAPCentre Anti‐PoisonCHRUCentre Hospitalier Régional UniversitaireeCRFelectronic Case Report FormICIQ‐UI‐SFInternational Consultation on Incontinence Questionnaire‐Urinary Incontinence Short FormIVOIntraVesical OxybutyninKIDSCREEN‐1010‐item KIDSCREEN questionnairePOXIPENPlace de l’OXybutynine Intravésicale chez le Patient Enfant Neurologique (Role of Intravesical OXybutynin in Neurological Paediatric Patients)RCTRandomised Controlled TrialUMUXUsability Metric for User eXperience

## Background

Lumbosacral pathologies, such as spina bifida, can affect bladder innervation and lead to a neurogenic bladder, often characterised by a non‐compliant, hyperactive, and small capacity bladder [1]. These dysfunctions usually lead to incontinence and obstruction of urine evacuation, eventually resulting in renal failure. The current therapeutic approach aims to improve urine evacuation and reduce intravesical pressure and progressively involves: (i) intermittent urinary catheterisation, (ii) oral anticholinergics, (iii) intradetrusor injections of onabotulinumtoxinA (Botox®, AbbVie Inc., North Chicago, IL, USA) and (iv) surgery.

As an anticholinergic, oxybutynin is usually prescribed orally. However, there are some contraindications and side effects associated with its oral administration, including important frequent neurological effects such as cognitive impairment [2], as well as a risk of drug resistance, requiring therapeutic escalation. The next step, intradetrusor injections of onabotulinumtoxinA, is invasive and must be performed under general anaesthesia in children. As for surgical procedures, although effective, they are irreversible and responsible for morbidity and mortality.

Since 1989 and the first study by Brendler et al. [3], the efficacy of intravesical oxybutynin (IVO) on detrusor overactivity and bladder hypocompliance has been reported in several studies [4, 5, 6, 7, 8, 9]. In 2008, a literature review conducted by Guerra et al. [10] focusing on children with a neurological condition who were resistant or had significant side effects with oral oxybutynin, showed improved bladder compliance and reduced bladder pressure with IVO. However, their level of evidence was not sufficient to support a change in practices. The 2016 study by Schröder et al. [11] was the first multicentre randomised controlled trial (RCT) comparing IVO with oral oxybutynin in adults. It showed excellent results, both in terms of efficacy in increasing bladder capacity, and security, with fewer side effects in the IVO group.

Although IVO appears to be a promising alternative to oral treatment in both adults and children, it is not yet included in international recommendations for the treatment of neurogenic bladder. The issue of therapeutic escalation, which leads affected patients, sometimes very young, to undergo multiple surgeries, is an important one, as the repeated use of general anaesthesia in children has been shown to affect their mental development [12, 13].

Actual recommendations on the management of neurogenic bladder in children – including guidelines from the European Association of Urology [14] – include the administration of anticholinergics as soon as possible, including in newborns [14, 15, 16]. However, in France, oxybutynin is, to date, only available in tablet form, which very young children may struggle to ingest. Another anticholinergic, solifenacin, is available in liquid form. Nevertheless, French authorities have considered the evidence insufficient to support its reimbursement for paediatric neurogenic bladder, unlike other countries in which solifenacin has been approved for paediatric use. Besides, and like other oral anticholinergics, solifenacin is still associated with systemic side effects, partly due to greater variability in serum concentrations [17, 18]. Other therapeutic alternatives, such as beta‐3 agonists (e.g., mirabegron) are also only available in tablet form and data on their efficacy in children remain limited. IVO would thus enable early anticholinergic treatment to be easily administered in newborns and young children undergoing intermittent catheterisation. In Germany, where IVO is already widely used in very young children who have failed oral anticholinergic therapy, its effectiveness seems highly promising and well accepted by patients and their families. However, it is not yet prescribed as an alternative to oral oxybutynin in other countries, such as France, in which it has only been granted a temporary authorisation for nominative use in March 2021.

As a consequence, we hypothesise that IVO may be a viable treatment option for the treatment of neurogenic bladder in paediatric patients who have failed anticholinergic therapy prior to a therapeutic escalation requiring an invasive procedure. We designed the ‘Place de l’OXybutynine Intravésicale chez le Patient Enfant Neurologique’ (POXIPEN; ‘Role of Intravesical OXybutynin in Neurological Paediatric Patients’) study, the first RCT to assess the efficacy of IVO on bladder capacity in a sample of French children with neurogenic bladder.

## Methods

### Study Design

The POXIPEN trial is a national multicentre randomised double‐blind placebo‐controlled trial, involving 19 French paediatric urological surgery departments. The list of the centres involved is available on Clinicaltrial.gov, where the trial is registered as NCT07027020.

### Objectives

The main objective of the POXIPEN trial is to assess the efficacy of IVO vs placebo on maximal bladder capacity in children with neurogenic bladder secondary to myelomeningocele (spina bifida), performing intermittent catheterisation, and for whom oral anticholinergic therapy has been deemed ineffective or associated with adverse effects.

Secondary objectives are:
To assess evolution of maximum bladder pressure after IVO (or placebo);To assess incontinence (i.e., time to clinical failure of treatment as perceived by the patient) after IVO (or placebo);To describe treatment tolerance and adverse effects;To assess the number of responders and continent patients after IVO (or placebo);To assess usability of IVO;To assess changes in patients’ quality of life after IVO (or placebo);To describe changes in patients’ voiding diary data after IVO (or placebo);To describe changes in urodynamic and in renal ultrasound parameters after IVO (or placebo);To identify patients’ characteristics associated with a greater likelihood of responding to IVO.

### Population and Sampling

The POXIPEN trial aims to include paediatric patients aged ≥6 years with neurological detrusor hyperactivity secondary to myelomeningocele (spina bifida) for whom oral anticholinergic therapy has been deemed ineffective or associated with adverse effects.

Inclusion criteria are as follows:
Age between 6 and 17 years;Detrusor hyperactivity secondary to spina bifida, confirmed by a urodynamic test carried out within the last 6 months, according to the International Children's Continence Society (ICCS) criteria [19];Use of intermittent catheterisation for at least 6 weeks and at least three times a day;Ability and willingness to perform catheterisation and intravesical instillation (patient or parents);Failed treatment with one or more anticholinergic agents, defined by a response deemed insufficient by the investigator after at least 4 weeks of treatment at optimal dose, inability to take oral oxybutynin, or adverse effects deemed intolerable by the patient and/or the investigator. Reason for deemed inefficacy or intolerance will be systematically recorded at the inclusion visit;Renal ultrasound carried out in the last 2 months;Cystomanometry (with maximum volume and maximum pressure) carried out in the last 6 months.

Exclusion criteria are:
Allergy to any component of the product under evaluation;Contraindication to oxybutynin (hypersensitivity, myasthenia, glaucoma, functional or organic gastrointestinal obstruction, severe gastrointestinal disease, subvesical obstruction, ongoing treatment with anticholinergic drugs for another indication that cannot be discontinued, polyuria of non‐vesical origin, concomitant oxygen therapy);Hyperthyroidism, coronary artery disease, congestive heart failure, cardiac arrhythmia, tachycardia, uncontrolled high blood pressure;Ongoing treatment with bisphosphonates, P450 cytochromes or cholinesterase inhibitors;Women of childbearing age without highly effective contraception, pregnant woman or nursing mother;Intradetrusor injection of onabotulinumtoxinA in the last 6 months.

All eligible patients will be screened for inclusion and exclusion criteria during a routine follow‐up visit to one of the participating centres. If a patient is being treated with oral anticholinergics, it will be stopped at the time of inclusion, to ensure a 7‐day wash‐out period before treatment initiation.

Randomisation will be performed by a centralised computer program, stratified by age group (6–11 years, ≥12 years) with the use of a permuted block design of size 10. Patients will be randomised to IVO vs placebo with a 1:1 allocation.

### Intervention

The experimental group will receive oxybutynin hydrochloride (VESOXX®, FARCO‐PHARMA GmbH, Cologne, Germany) at a concentration of 1 mg/mL in 10 mL syringes ready for intravesical instillation for 4 weeks. The treatment will be instilled at the end of evacuation catheterisation, and the solution will be retained in the bladder until the next scheduled catheterisation, with a minimum dwell time of 30 min to ensure sufficient mucosal exposure. The total daily dose will be 0.4 mg/kg/day. If the calculated per‐instillation dose does not exceed 10 mg, the daily dose will be divided into two instillations. If it exceeds 10 mg per instillation, the daily dose will be divided into three equal instillations, to remain within the per‐dose cap. The maximum daily dose will be 20 mg/day for patients aged <12 years, and 30 mg/day for patients aged ≥12 years. The first administration will be carried out by a hospital nurse in a double‐blind setting during a therapeutic education session. Subsequent instillations will be carried out by the patient or his/her parents. To ensure consistency, instillations will be spaced at approximately 12‐h intervals (±2 h) when two instillations are required, and at approximately 8‐h intervals (±3 h) when three instillations are required. This compromise allows for standardisation of dosing intervals while accommodating family and school logistics. The usual catheterisation schedule will not be modified, in order to avoid altering bladder behaviour and to enhance acceptability for families.

The control group will receive the same volume of 0.9% sodium chloride in the same modalities as the intervention group. As the modalities of administration and packaging will be the same in the two arms, neither the patient, the investigator nor the monitor will be informed of the treatment assigned.

### Endpoints

The primary outcome is change in maximum bladder capacity after 4 weeks of treatment (end of follow‐up). This parameter is considered by experts to be an objective marker of improvement in neurogenic bladder. It will be measured by cystomanometry and is defined by the maximum bladder volume (mL) recorded after filling via the urethral catheter, which may occur under one of the following conditions: (i) when the patient is given permission to urinate, (ii) when detrusor pressure reaches 40 cmH₂O, (iii) when the expected maximal bladder volume for age is reached, or (iv) when the patient reports an irrepressible urge to urinate. In younger patients, urination occurs spontaneously, and this value will be obtained *a posteriori* by curve analysis. Change will be assessed between two measurement times: one before initiation of treatment, performed <6 months prior (i.e., reference cystomanometry), at best in the absence of oral anticholinergic treatment, and the other at the end of treatment, under the same conditions. Cystomanometers will be calibrated at the start of each procedure.

Secondary outcomes will be:
The 4‐week change in maximum bladder pressure, measured by cystomanometry.Time to treatment failure within 28 days, defined on the basis of criteria available in the literature (at least one of three criteria):
Treatment deemed ineffective by the patient or practitioner;A <50% reduction of incontinence episodes reported in the voiding diary;Intolerable side effects reported by the patient.
Occurrence of adverse events (AEs; including digestive, psychiatric, neurological, skin, urological and pain‐related disorders) and their time of onset, as recorded by the patient in his/her treatment journal (Data S1) or by the practitioner during follow‐up visits.Proportion of responders, i.e., patients who had a ≥50% reduction in urinary incontinence episodes recorded in their voiding diary [20], after 4 weeks of treatment, with no intolerable AEs.Proportion of continent patients, i.e., patients who had a 100% reduction in urinary incontinence episodes, after 4 weeks of treatment [20].Standardised difference in patient's quality of life, as assessed by changes in the International Consultation on Incontinence Questionnaire‐Urinary Incontinence Short Form (ICIQ‐UI‐SF) [21] and the 10‐item KIDSCREEN questionnaire (KIDSCREEN‐10) [22] scores between the inclusion visit and the end of follow‐up.Changes in voiding diary parameters, as assessed by the change in the number and volume of urinary catheterisations over 72 h during the week preceding each follow‐up visit. If treatment is effective, voided volume should increase.Changes in urodynamic parameters between the reference cystomanometry and the cystomanometry performed at the end of treatment:
Bladder compliance (mL/cmH_2_O),Minimum filling volume causing uninhibited detrusor contraction,Detrusor leak point pressure (cm H_2_O),Volume of bladder filling during urine loss (mL).

To ensure consistency and standardisation across centres, all participating investigators will be asked to perform both cystomanometries under the same conditions for each patient, regarding bladder filling rates and patient positioning.
Changes in renal ultrasound parameters between the reference renal ultrasound (performed <2 months prior to treatment initiation), and the one performed at the end of treatment:
Pyelon anteroposterior diameter (mm),Ureter diameter (mm).

If treatment is effective, a reduction in both diameters could be observed, as a result of the decrease of pressure in the renal system.
Usability of the product, measured by the Usability Metric for User eXperience (UMUX)‐LITE scale [23] coupled with seven ad hoc questions specific to the treatment and disease under study, measured on a 7‐point Likert scale (from strongly disagree to strongly agree; Data S2).

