### Data Collection and Patients’ Follow‐Up

Three follow‐up visits are planned for each patient. Visit 1 (i.e., Day 1 of treatment) will include a measurement of quality of life using the ICIQ‐UI‐SF and KIDSCREEN‐10 questionnaires, a clinical examination, and an evaluation of the voiding diary completed over a 72‐h period before the visit. The treatment kit assigned by the centralised randomisation system will be given to the patient to cover the 4 weeks of treatment, and the first administration will be performed by a nurse, after a therapeutic education session. Each patient will receive a treatment journal to record the information needed to monitor compliance (dates and times of administration, observations), as well as adverse effects. If the patient is a child, parents will be asked to complete the document.

Visit 2 will take place after 2 weeks of treatment. It will include a clinical examination and an evaluation of the voiding diary and treatment journal.

Visit 3 will take place at the end of the 4 weeks of treatment. It will include a clinical examination and an evaluation of the voiding diary and treatment journal. If the patient has already discontinued the treatment before the visit, the date of discontinuation will be noted. Otherwise, the treatment will be interrupted on this visit. A cystomanometry will be carried out under the same conditions as the one carried out before the inclusion visit, as well as a renal ultrasound. Quality of life and usability of the product will be assessed.

A urine pregnancy test will be performed at each visit in female patients of childbearing age.

Between visits, patients will be asked to record the number and volume of catheterisations, as well as urine leakage for 72 consecutive hours in their voiding diary provided during the inclusion visit (Data S3).

Treatment or placebo may be stopped prematurely at any time in case of serious adverse effect, if the investigator deems it necessary for the patient's safety, or if the patient wishes to discontinue treatment. In this case, only the next scheduled visit is maintained (i.e., Visit 2 or 3) and the procedures planned for Visit 3 will be carried out to collect outcomes. The patient will continue to receive usual medical care.

A follow‐up call will be scheduled 7 days after the last consultation, to assess any residual effect of the treatment or placebo.

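### The reference cystomanometry may be done on oral anticholinergics that are stopped before treatment, so the primary change score can mix loss of the old drug with the effect of IVO or placebo

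*Protocol article*

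**What the plan says.** The Protocol article's Endpoints section defines the primary outcome as a change between two cystomanometries. The first, the reference test, is done less than 6 months before treatment starts, and the section sets the terms for both tests as follows: "at best in the absence of oral anticholinergic treatment, and the other at the end of treatment, under the same conditions". Data Collection and Patients' Follow-Up repeats this for Visit 3: "A cystomanometry will be carried out under the same conditions as the one carried out before the inclusion visit". The only place that spells out what has to match is the standardisation paragraph later in Endpoints, which has both tests done alike "regarding bladder filling rates and patient positioning". Drug state is not mentioned there.

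Population and Sampling requires "Cystomanometry (with maximum volume and maximum pressure) carried out in the last 6 months". On current oral treatment it says: "If a patient is being treated with oral anticholinergics, it will be stopped at the time of inclusion", to give a 7-day wash-out before study treatment. Visit 1, as described, has no cystomanometry.

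The primary model in Statistical Analyses lists repeated measurement, age stratum and treatment. It names no term for drug state at the reference test.

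**The concern.** A child whose reference test was done on an oral anticholinergic starts from a capacity that the drug may have enlarged. If that child stays on study treatment, the week-4 test is off the oral drug. The change then has two parts: what was lost when the oral drug stopped, and what IVO or placebo did. Matching filling rate and position does not remove the first part.

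Such children are plausible. The protocol foresees some still on oral treatment at inclusion, and it admits children for intolerable adverse effects as well as for poor response. In a child who enters for intolerance, the oral drug may have worked on the bladder.

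At stake are the precision of the primary comparison, which rests on an assumed within-child correlation of 0.8, and the meaning of each arm's mean change, which is how Sample Size states its expectations (33% and 5%). The same reference test supplies maximum bladder pressure, the first outcome in the fixed sequence, and the other urodynamic changes.

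**Working it through.** **Inputs from Sample Size:** baseline mean 170 mL, SD 80 mL, correlation 0.8, increases of 33% and 5%, power 0.9, type I error 0.05 (two-sided assumed; the article does not say), 26 per group, rounded up to 60 in total, i.e. 30 per group.

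**The plan's own figure**
- Expected changes: 0.33 × 170 = 56.1 mL and 0.05 × 170 = 8.5 mL; difference 47.6 mL.
- SD of change: 80 × √(2 × (1 − 0.8)) = 50.6 mL; variance 2560.
- Patients per group for 90% power: 24 (normal approximation) or 25 (noncentral t). The stated 26 is within two of these.
- Power by noncentral t: 0.914 at 26 per group, 0.948 at 30.

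**Adding an on-drug reference test.** Let a share f of children be tested on drug, and let the drug raise their reference capacity by a constant e mL that is absent at week 4. The 170 mL is taken as the off-drug mean. Neither f nor e is given in the article. The range for e is 10%, 20% and 33% of 170 mL; the top value is the capacity increase that Sample Size cites from a tolterodine study in the target population. With f = 0.5:
- Shift in each arm's mean change: −f × e.
- Variance of change: 2560 + f(1 − f)e².
- Implied correlation: 5120 / (80 × √(6400 + f(1 − f)e²)), where 5120 = 0.8 × 80².

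| e (mL) | Variance | SD of change | Correlation | Power, 30 per arm | IVO change | Placebo change | Difference |
|---|---|---|---|---|---|---|---|
| 0 | 2560 | 50.6 | 0.800 | 0.948 | +56.1 | +8.5 | 47.6 |
| 17 | 2632 | 51.3 | 0.796 | 0.942 | +47.6 | 0.0 | 47.6 |
| 34 | 2849 | 53.4 | 0.783 | 0.925 | +39.1 | −8.5 | 47.6 |
| 56.1 | 3347 | 57.9 | 0.755 | 0.880 | +28.1 | −19.6 | 47.6 |

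The difference column does not move, because the shift is the same in expectation in both arms. The within-arm columns move a good deal: in the two larger scenarios the placebo group appears to get worse.

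**Smaller shares.** With e = 56.1 mL, power at 30 per arm is 0.898 for f = 0.25 and 0.906 for f = 0.20.

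**With the fix.** Under the constant-shift assumption, adjusting for the yes/no drug state removes the f(1 − f)e² term. The SD of change returns to 50.6 mL and power at 30 per arm to about 0.947, after one or two degrees of freedom are spent.

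**The case against.** The strongest reply is that the primary analysis is a randomised comparison and the reference test comes before randomisation. Drug state at that test is balanced in expectation and the expected difference stays at 47.6 mL. This stands. A reader might infer from a contaminated change score that the treatment effect is biased; the design does not support that.

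The second reply is that the precision loss is small at the size actually planned. This also largely stands. At 30 per arm two of the three scenarios stay above 0.90. The third combines the share that maximises f(1 − f) with the full 33% effect, in a population where poor oral response is one route of entry. If the mixed model uses baseline as efficiently as an analysis of covariance would, that scenario still has power of about 0.93. The point therefore does not show that the sample size is inadequate, nor that the correlation collapses: the lowest implied value is 0.755.

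Third, the same-conditions wording can be read as covering only filling rate and position, which every child can meet. That is a fair reading, but it leaves drug state uncontrolled, which is the gap described here.

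Fourth, it would be too strong to say that the final test is never on an oral anticholinergic. Children who stop early return to usual care, and the text neither allows nor bars an oral drug by their final test.

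Finally, the eCRF is not shown, so a drug-state field may already exist. That would make the fix cheaper; it would not put the term in the model.

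**Conclusion.** The point holds in a limited form. The documents allow an on-drug reference test, stop the drug before treatment, describe no test in between, and fix a primary model without a term for it. The randomised contrast is unbiased in expectation. The cost is a modest loss of precision (power at 30 per arm from 0.948 to 0.942 / 0.925 / 0.880) and a downward shift of about 8.5 / 17 / 28 mL in both arms' mean change. These sizes rest on an assumed 50% of tests on drug and an assumed constant effect of 10 / 20 / 33% of 170 mL. The within-arm shift is the more visible consequence: a reader of the results could take IVO to be weaker, and placebo more harmful, than they are.

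A narrower, secondary point concerns botulinum toxin. The exclusion reads "Intradetrusor injection of onabotulinumtoxinA in the last 6 months", and the window for the reference test is also 6 months. An injection 7 months before screening and a reference test 5 months before screening would both be allowed, which puts the test 2 months after the injection. So the exclusion does not strictly protect the reference test. A reader might infer that this is common. The documents do not support that: the protocol places IVO before that escalation, and the case is inferred only from two equal windows. It is not part of the figures above.

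**What to change.** 1. Record whether the child was taking an anticholinergic on the date of the reference cystomanometry.
2. Where several tests exist within the 6 months, name the latest off-drug one as the reference, and fix the choice before randomisation.
3. Add the yes/no drug-state indicator to the primary model and to the maximum-pressure model. If baseline is modelled as an outcome, include the indicator's interaction with time: the main effect alone would not remove the shift in change. The indicator is fixed before randomisation, so adjusting for it is safe.
4. Report the treatment effect in children with an off-drug reference test as a sensitivity analysis, and describe within-arm change by drug state.
5. Reconcile the same-conditions wording in Endpoints and in Data Collection and Patients' Follow-Up with the stopping rule in Population and Sampling, and say whether the phrase covers drug state.
6. Record the date of any previous intradetrusor injection as a separate item. Do not pool it with oral drug use, since the two effects differ.

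The cost is one or two eCRF fields, in an eCRF that the article reports as complete, and one or two degrees of freedom. No child needs an extra procedure and the sample size does not change.

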### Statistical Analyses

For the primary outcome, an intention‐to‐treat analysis will be conducted to assess the difference between the two groups in the evolution of maximum bladder capacity, using a linear mixed model accounting for repeated measurement, age stratification, and treatment exposure as a binary variable. A secondary exploratory analysis will be conducted to account for any imbalance that may occur between groups despite randomisation due to the small sample size. Multivariate linear regression will be performed, adjusted for age and gender.

Given the small sample size and the short duration of follow‐up for each patient, there should be little or no missing data. For the primary outcome, patients lost to follow‐up will be assigned the value measured during the last cystomanometry performed (i.e., last observation carried forward).

No intermediate analysis is planned given the small sample size.

Two secondary outcomes will be analysed following a fixed sequence in a priori ordered hypotheses:
Maximum bladder pressure after 4 weeks of treatment: the two groups will be compared using the same methodology as for the primary outcome;Time to treatment failure: the two groups will be compared using a two‐tailed log‐rank test. If a patient is lost to follow‐up, the date of treatment failure will be the date of last news plus 1 day.

Occurrence of AEs will be compared in the two groups using a Fisher's test with a significance threshold = 0.05.

The proportions of responders and continent patients after 4 weeks of treatment will be calculated with their 95% CI.

Standardised differences in patients’ quality of life assessed with the KIDSCREEN‐10 and ICIQ‐UI‐SF questionnaires will be compared between the two groups using a Wilcoxon test, with a significance threshold = 0.05. As recommended by the KIDSCREEN‐10 developers, an additional subgroup analysis will be performed to distinguish children aged 6–7 years from those aged 8–17 years.

Changes in voiding diary elements, urodynamic parameters, and renal ultrasound parameters after 4 weeks of treatment will be compared using a Wilcoxon test, with a significance threshold = 0.05.

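### Three secondary urodynamic changes have no value when no contraction or leak occurs during filling; for first-contraction volume the Wilcoxon test would then tend to omit treatment successes

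*Protocol article*

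**What the plan says.** The Protocol article, Endpoints, sets four urodynamic parameters as secondary outcomes, each taken as "Changes in urodynamic parameters between the reference cystomanometry and the cystomanometry performed at the end of treatment". Bladder compliance needs no event during filling. The other three do: "Minimum filling volume causing uninhibited detrusor contraction,Detrusor leak point pressure (cm H_2_O),Volume of bladder filling during urine loss (mL".

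The same section, in defining maximum capacity, gives the conditions under which the final volume may be recorded. Two of them are "when detrusor pressure reaches 40" cmH₂O and "when the expected maximal bladder volume for age is reached"; irrepressible urge is another. A test can therefore finish with no contraction or no leak.

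Under Population and Sampling, entry requires "Detrusor hyperactivity secondary to spina bifida, confirmed by a urodynamic test carried out within the last 6 months". No leak on cystomanometry is required.

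Under Statistical Analyses, "Changes in voiding diary elements, urodynamic parameters, and renal ultrasound parameters after 4 weeks of treatment will be compared using a Wilcoxon test", at a threshold of 0.05. That section expects little or no missing data. Its carry-forward rule covers only the primary outcome and only patients lost to follow-up. The document gives no value or rank to a child who attends, is tested and shows no event.

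**The concern.** A change needs a number at both tests. If the end-of-treatment filling runs to the expected volume with no uninhibited contraction, the volume at first contraction does not exist and neither does its change. Applied to the endpoint as defined, the Wilcoxon test has nothing to rank for that child.

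This is not ordinary missing data. An anticholinergic instillation is meant to suppress the contraction, so its absence at week 4 is often the wanted result and should be commoner on IVO than on placebo. The children left in the comparison are then selected after randomisation by their response. What is at stake is a secondary result that could look weak or null because the treatment worked in some children.

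The leak endpoints share the definitional gap but not its simple interpretation. A leak value can be absent because the child did not leak at the reference test, because filling stopped on pressure or urge before a leak, or because leakage was suppressed.

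**Working it through.** **1. The plan's own figure.** The protocol gives a sample size for the primary outcome only. Inputs from Sample Size: baseline 170 (SD 80) mL, increases of 33% and 5%, correlation 0.8, power 0.90, alpha 0.05 (two-sided assumed).

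- Difference: 170 × (0.33 − 0.05) = 47.6 mL
- SD of change: 80 × √(2 × (1 − 0.8)) = 50.6 mL
- n per group: 2 × (1.960 + 1.282)² × 50.6² / 47.6² = 23.7, so 24; the t-test version gives 24.7, so 25

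The stated 26 is reproduced to within two patients, and this point does not touch it. No event rate, effect or SD is given for the urodynamic endpoints, so everything below is illustrative.

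**2. When each change exists.**

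| Endpoint | Needed at both tests | Ways to have no value |
|---|---|---|
| Compliance | no event | not affected |
| First-contraction volume | contraction | contraction suppressed; filling stopped before it |
| Leak point pressure | leak | no leak at baseline; stop at 40 cmH₂O or at urge; leak suppressed |
| Volume at urine loss | leak | the same |

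**3. Size for first-contraction volume.** Assumptions: 30 per arm; mean change 25 mL on IVO and 5 mL on placebo (true difference 20 mL); SD 45 mL; contraction abolished in 5% on placebo and in a share q on IVO; latent correlation 0.6 between abolition and gain in volume.

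With φ and Φ the standard normal density and distribution function, omitting a share q lowers an arm's expected mean by 0.6 × 45 × φ(z) / (1 − q), where z = Φ⁻¹(1 − q).

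- Placebo, q = 5%: 27 × 0.1031 / 0.95 = 2.9 mL
- IVO, q = 10%: 27 × 0.1755 / 0.90 = 5.3 mL; difference 20 − 5.3 + 2.9 = 17.6 mL
- IVO, q = 30%: 27 × 0.3477 / 0.70 = 13.4 mL; difference 20 − 13.4 + 2.9 = 9.5 mL

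Simulated power of the Wilcoxon (Mann-Whitney) test under the same model:

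| Abolished on IVO | Complete cases | 'No contraction' ranked best | All values observed |
|---|---|---|---|
| 10% | 31% | 38% | about 38% |
| 20% | 21% | 49% | about 38% |
| 30% | 11% | 62% | about 38% |
| 40% | 7% | 78% | about 38% |

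The fair reference for the loss is the last column. Ranked power above 38% comes from the assumed difference in abolition itself, which the complete-case test discards. With zero correlation and 30% abolition, the complete-case difference stays at 20 mL, so there is no bias in it; power is about 31% against 82% ranked.

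**4. A second model.** Here the event is unseen whenever its volume exceeds the stopping volume. Assumptions: baseline event volume 120 (SD 50) mL, shift 47.6 mL, SD of change 50.6 mL, 30 per arm. The all-values difference is about 46 mL and all-values power about 93%.

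| Stopping volume | Evaluable IVO / placebo | Complete-case difference | Complete-case power |
|---|---|---|---|
| 400 mL | 30 / 30 | 46 mL | 93% |
| 300 mL | 29 / 30 | 44 mL | 93% |
| 250 mL | 26 / 29 | 41 mL | 89% |
| 200 mL | 20 / 25 | 35 mL | 73% |
| 180 mL | 17 / 23 | 32 mL | 63% |

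Both models point the same way for a volume endpoint. Both also show that the effect is negligible when few children lose the event.

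**The case against.** The strongest reply is that no sentence excludes these children. A Wilcoxon test can rank 'no event' as best, so the named test is compatible with sound handling, and coding an absent event is the kind of detail an analysis plan or case report form often carries. It is right that exclusion is a consequence and not a stated rule. It does not remove the point: the endpoint is defined as a change between two measured values, and for a child whose contraction has gone that definition yields nothing to rank.

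A reader might infer that all three endpoints lose exactly the best responders and are all biased against IVO. The documents do not support that. Filling may stop at 40 cmH₂O or at urge before a leak, and such a child is not a success. Entry does not require a leak, so values may be absent at baseline in both arms. For the same reason, ranking every 'no leak' as best would put some pressure-stopped bladders, and children who leaked at neither test, at the top.

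It is also fair that the rates are assumed, that the effect is small at 10% abolition, and that the objective for these parameters is descriptive. Compliance, maximum pressure and maximum capacity need no event, and continence is captured by the diary-based proportions. These limits bear on the weight of the point, not on whether it exists.

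**Conclusion.** The point holds in a limited form. As defined, the three changes cannot be computed when the event is absent at either test, and the filling rules allow that.

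For first-contraction volume, a missing week-4 value will often mean success, so the comparison tends to be biased toward no effect. This rests on the hyperactivity entry criterion and on abolition going with larger gains in volume. If abolition is unrelated to gain, the difference among the remaining children is unbiased and only information is lost.

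For the two leak endpoints the comparison is on a selected subset with mixed causes of absence. For leak point pressure the direction of bias is uncertain. The simulations do not size either leak endpoint.

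The loss for first-contraction volume runs from small (31% against 38% power at 10% abolition) to large (11% against 62% at 30%, with about 38% if every value were observed), all under assumed rates. A claim that the urodynamic objective cannot be answered, or that the trial's main conclusion is at risk, would go too far: the primary outcome and the fixed sequence (maximum pressure, then time to treatment failure) are unaffected. It is worth correcting because the correction is cheap.

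**What to change.** In Endpoints and Statistical Analyses:

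- **Record** 'no contraction' and 'no leak by end of filling' as results at both cystomanometries, with the reason filling stopped and the final volume.
- **First-contraction volume:** rank 'event at baseline, none at week 4' as the most favourable outcome when filling reached the expected volume. Otherwise treat the week-4 value as censored at the final filling volume. A generalised (Gehan) Wilcoxon test can handle both.
- **Volume at urine loss:** do the same only in children who leaked at baseline, and do not rank a pressure-stopped test as best.
- **Leak point pressure:** describe it among children who leak, without a between-arm test.
- **Report by arm** the proportions with no contraction and with no leak at both tests.

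The cost is wording for three secondary endpoints and one or two extra fields in the electronic case report form. That form is reported as complete, so check whether it already holds them. No extra procedure or patient is needed. The small downside is a rank or censored comparison in place of a difference in mL.
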